### 2.6.2 Children

In children weighing  $\geq 10$  kg, the doses will be adapted to the body weight. Using the population model developed by Toyama Chemical, the disposition in pediatric patients aged more than one year is predictable from adults using weight-based allometric scaling. Weight-based favipiravir doses for children were then determined in order to reproduce similar adult drug levels (to reach quick satisfactory concentration and lead to a median state trough concentration of 57  $\mu\text{g/mL}$ ) are shown in Table 1.

**Table 1. Recommended Weight-based favipiravir doses in children with EVD.**

| Weight (kg)  | Day-0 (mg) |      |      | Day-1 to Day-9 (mg) |      |     |
|--------------|------------|------|------|---------------------|------|-----|
|              | 0h         | 8h   | 16h  | 0h                  | 8h   | 16h |
| 10 - 15      | 500        | 500  | 200  | 200                 | 200  | 200 |
|              | Day-0 (mg) |      |      | Day-1 to Day-9 (mg) |      |     |
|              | 0h         | 8h   | 16h  | 0h                  | 12h  |     |
| 16 - 21      | 800        | 800  | 400  | 400                 | 400  |     |
| 22 - 35      | 1200       | 1200 | 600  | 600                 | 600  |     |
| 36 - 45      | 1600       | 1600 | 800  | 800                 | 800  |     |
| 46 - 55      | 2000       | 2000 | 1000 | 1000                | 1000 |     |
| > 55 (adult) | 2400       | 2400 | 1200 | 1200                | 1200 |     |

Justification of the choice of dosage regimen in children has been accepted for publication (Bouazza N *et al.*, 2015).

### 2.7 Treatment duration

The duration of the viremic period in patients with EVD is 10 days (Ksiazek *et al.* 1999). In addition, in severely affected patients, profound immunosuppression may occur early after the disease onset, and we do not know whether this would still be the case or not in patients receiving the antiviral. Therefore, we chose to provide favipiravir during 10 days, to ensure optimal probability of success. If the control of viremia occurs early and leads to substantial clinical improvement, shorter duration could be considered in further studies.

## 2.8 Toxicity issues

### 2.8.1 Adults

So far, about 2000 subjects received at least one dose of favipiravir during the clinical development of the drug for the treatment of influenza. Among them, several hundred received a loading dose of 3600 mg (1800 mg bid or 2400 mg, 600 mg, 600 mg administered on an 8h schedule). Side effects were rare, and included diarrhea (2.8%), asymptomatic hyperuricemia (1.5%), asymptomatic increase in liver enzyme (AST, ALT, gamma-GT) (1.3%), asymptomatic decrease in neutrophil counts and white blood cells, headache, asymptomatic increase in triglycerides (1%), vomiting, dizziness and proteinuria (0.9% each). Details from the investigator's brochure are available in Appendix 6.

Based on non clinical data, three additional issues have been raised:

- QT prolongation: positive findings were shown on the hERG channels. Consequently a dedicated QT/QTc study was performed in healthy adult volunteers with a single dose of 2400 mg. Although this study was negative, the potential risk of QT prolongation cannot be strictly ruled out in the context of EVD (higher doses, diarrhea with dyskaliemia).
- Pregnancy: early embryonic deaths and teratogenicity were reported in animal studies (Baranovich *et al.* 2013). In consequence, favipiravir is not recommended in women known to be pregnant, and it is recommended that women of child bearing potential be tested for pregnancy before receiving the drug. Because of this, the sponsor could not find any insurance company keen to insure pregnant women participating in the trial. However, in the largest case series published (Mupata *et al.* 1999) the mortality in EVD-infected pregnant women was 93% (14 out of 15 pregnant patients died in an outbreak in DRC). The one patient who survived delivered a preterm dead fetus. The perinatal mortality in this publication was 100%. One infant was born alive but died after three days (Mupata *et al.* 1999). Johnson *et al.* also in DRC in 1978 reported a mortality rate in pregnant women of 89 % (73 out of 82 pregnant women with EVD died) and there were no survivors among the neonates. Up till now no reports have been published of neonates born to mothers with EVD surviving more than 3 days (Jamieson *et al.* 2014). Given these outcomes of EVD in pregnant women and MSF unpublished data from the current epidemic (mother death, or spontaneous abortion if the mother survives), the benefit/risk ratio of receiving the drug has been deemed to be likely positive for both the mother and the baby. Thus, emergency use of favipiravir in pregnant women outside of the trial is envisaged and under evaluation.
- Fertility: favipiravir passes into the sperm. Testicular findings were reported in animal, which led to perform a testicular study in human (1200 mg bid on Day-1, followed by 800 mg bid for 4 Days). The results did not show significant impairment on seminal parameters.

### 2.8.2 Children

So far no children have been exposed to favipiravir. Juvenile toxicity animal's studies have shown higher level of toxicity with lower exposure as compared to adult animals. However, it is difficult to extrapolate these findings to children.

Below 12 months of age and below 10 kg, drug disposition is difficult to predict for favipiravir. Therefore, we will not include infants below 12 months or below 10 kg in order to avoid inaccurate prediction of drug levels and limit the potential risk of drug overdose.

## 2.9 Context implications

The investigators of the present trial subscribe to the MSF principle that a research program should not have negative impact on patients care and need to be time/context adapted from start to end.

This trial takes place in a very unusual context:

- A highly contagious fatal disease where every additional medical gesture entails additional risks to health care staff;

- A huge complexity to organize effective prevention and care with multiple factors and conditions of care that may evolve within time according to programmatic decisions;
- A volatile emergency epidemic situation, in which the number of cases in a given center can change very fast;
- An international community mobilization that could lead knowledge to evolve rapidly, a situation to which researchers should adapt in real-time.

This context influences the trial in the following ways:

- The trial has to fit in a simplest possible way into the conditions organized by the care givers and organizers (Ministry of health, NGO, other institutions). In particular:
  - additional body fluid collection and sample manipulations prior to cryoconservation, should be limited to the bare minimum;
  - data collection should be simple, with no circulation of material (such as CRFs) from the inside towards the outside of the centers;
  - statistical power considerations impose to conduct the main analysis on data from the group of patients in whom the treatment benefit is expected to be the greatest; however, any individual with EVD and no contraindication to favipiravir who is taken care of in the same trial center should have access to the drug if s/he may potentially benefit from it, even if s/he does not belong to the group in whom the treatment benefit is expected to be the greatest;
  - once favipiravir has been added to the current care, any other decisions regarding modification of the current care practices should be taken with the care actors, and only if they are considered necessary to improve care (not for the very sake of the trial).
- Particular attention should be paid to the risks for trial staff and health care personal. This imposes to eventually consider post-exposure prophylaxis with favipiravir, even in the absence of previous evidence of its efficacy, and to have a clear procedure for high standard of care in the event of an exposed personal becoming infected with EBOV. The best known post-exposure prophylaxis regimen is under evaluation.

### 3. Objectives

**Primary objective:** to assess the efficacy of high-dosed favipiravir in reducing mortality in humans with EVD

**Secondary objectives:** to assess the efficacy of high-dosed favipiravir in reducing mortality in humans with EVD according to age and baseline viral load; to assess the evolution of EBOV plasma RNA and infectious loads under treatment; the tolerance of favipiravir; the viral micro-diversity of EBOV; the trough concentrations of favipiravir; and factors associated with mortality and toxicity.

### 4. Study design

Non-comparative, proof-of-concept, phase II trial.

### 5. Study sites

The trial will take place in several EVD care centers in Guinea.

It will start in December 2014 in the MSF EVD care center in Gueckedou.

Depending of the inclusion rate and on the evolution of the outbreak, other EVD care centers will join in and become trial centers in January 2015: the French Red Cross EVD care centre in Macenta, the ALIMA EVD care centre in Nzerekore, the caregivers treatment center (STC) managed by the health services of the French aries, the MSF EVD care center in Donka, the MSF EVD care center in Cancan, and the EVD care center in Coyah.

## 6. Participants

### 6.1 Inclusion and non-inclusion criteria

**Inclusion criteria:** age  $\geq 1$  year and weighting  $\geq 10$ kg, EVD confirmed by a positive qualitative PCR test, signed informed consent (signed by the parents/adults guardians in case of minor patient).

**Non inclusion-criteria:** pregnancy\*, inability to take the drug (encephalopathy, severe vomiting).  
(\*for pregnant women, see sections 2.8).

### 6.2 Groups

In this protocol, we will refer to the following groups according to age and duration of symptoms\*:  
Group A1: adults with time between first symptoms and first dose of favipiravir  $\leq 72$ h; Group A2: adults with time between first symptoms and first dose of favipiravir  $> 72$ h and Group C: all children  $\geq 1$  year and weighting  $\geq 10$ kg. Time of first symptom refers to the time of the beginning of any symptom considered to be related to EVD.

\* Symptoms to be considered will be: acute onset of fever, severe headache, myalgia, extreme fatigue, vomiting, diarrhoea, abdominal pain, or unexplained hemorrhage.

The division in groups is a matter of analysis, and will not be perceptible by the patients during the trial process. Patients in the three groups will receive the same treatment and will be followed under the same procedures. Daily dosages will be adapted to the body weight in group C.

A second definition of group was also used: group AC1: adults and children  $> 6$  years with baseline Ct  $\geq 20$ ; group AC2: adults and children  $> 6$  years with baseline Ct values  $< 20$ ; group YC: young children  $\leq 6$  years and  $\geq 1$  year.

### 6.3 Sample size and power

Because we expect the efficacy of the treatment to be the maximum in patients with early symptoms, the sample size calculation was based on the analysis of mortality in group A1.

The observed pre-trial mortality was estimated using the three months pre-trial data of the MSF Macenta EVD Transit Center and the MSF Gueckedou EVD Care Center from Sept 15, 2014 to Dec 14, 2015. Given those observations, and to remain pragmatic and conservative, we set the pre-trial mortality to 55% for groups A1, A2, C, and to 30%, 85%, 70% for groups AC1, AC2, YC, respectively.

With 60 participants in group A1, the power to conclude that mortality in the trial will be -20% inferior to pre-trial mortality will be equal to 89%.

Recruitment will be kept opened in all groups until 60 patients are recruited in Group A1, unless otherwise recommended by the DSMB (*see stopping rules in section 9.3*). Once 60 patients are included in Group A1, recruitment will stop in all groups, irrespective of the number of patients included in other groups. When recruitment stops, new patients who show up next will either receive favipiravir or another treatment within the framework of the next phase of the research (*see section 10*). There will be no gap between the present trial and the next phase of the research.

We estimate that 80% of adults with suspected EVD and symptoms will be confirmed to have EVD with a positive PCR. Thus, 75 patients will be eligible to group A1 (including 15 with negative PCR who will not be included, and 60 with positive PCR who will be included in analysis). The number of patients in groups A2 and C will depend on the proportion of adults showing up with  $\leq 72$ h symptoms and on the proportion of children in the population of patients with EVD referred to the three trial settings during the study period.

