**Blood collection:**

- Adults (groups A1 and A2): blood will be collected in 4 ml trial tubes during: (i) routine care venepuncture (Day-0; end of symptoms (EOS)+72h); (ii) additional trial venepuncture at: Day-2, Day-4, Day-13 and Day-30.
- Children (group C): blood will be collected in 4 ml trial tubes during: (i) routine care venepuncture (Day-0, EOS+72h); (ii) additional trial venepuncture at Day-2 Day-4, Day-13 and Day-30.

**Biology:** *In trial settings laboratories:* At Day-0, Day-2 Day-4, Day-13 the following tests will be done: qualitative PCR (Altona qualitative RT-PCR commercial kit); and biochemical tests (creatininemia and others tests according to local choice), if biochemical tests are doable in the laboratory. At Day-30 the following tests will be done: biochemical tests (creatininemia and others tests according to local choice) only if tests at Day-13 were abnormal *Outside trial settings laboratories:* all trial tube will be shipped frozen in triple-layer packaging to the Lyon-Mérieux BSL4 laboratory, where the following tests will be done: quantitative PCR (standard real-time RT-PCR procedures, synthetic RNA quantified external calibrators), infectious viral load (standard procedure with serial sera dilutions and infection of Vero cells), viral subpopulations (next-generation sequencing methods), drug concentrations measurement (HPLC), uricemia, and other biochemical tests (transaminases, creatininemia, natremia and kaliemia), if biochemical tests have not been done in the trial setting laboratory.

**Sample size:** recruitment in the trial will be kept opened in all groups\* until group A1 reaches 60 participants (\*unless early termination is recommended by the DSMB).

**Statistical analysis for primary outcome:** mortality by Day-14 with exact 95%CI will be reported overall and in each group separately.

In group A1, if the number of deaths is <24 (40%) out of 60 participants, the upper bound of the 95%CI will be <55%.

In group A2, if the number of deaths is <54 (45%) out of 120 participants, the upper bound of the 95%CI will be <55%.

In group C, if the number of deaths is <17 (38%) out of 45 participants, the upper bound of the 95%CI will be <55%.

In each group (A1, A2, C), we will conclude that favipiravir decreases mortality if the upper bound of the 95% CI does not include the observed pre-trial mortality (55%) in untreated patients with same duration of symptoms prior to trial initiation.

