## **9. Statistical analysis**

### **9.1 Mortality**

Mortality at Day-14 will be reported with its exact 95% confidence intervals (CI), overall, and separately by groups (A1, A2, C).

The analyses will be performed first using the intention to treat approach, including all patients with positive PCR who received at least one dose of favipiravir. In case of missing data for mortality at Day-14 patient will be considered dead.

A per protocol analysis will then be performed, including all patients who received the treatment until Day-9 or death.

In each group, we will conclude that favipiravir decreases mortality if the upper bound of the 95% CI does not include the observed pre-trial mortality in untreated patients with same duration of symptoms prior to trial initiation (*see section 6.3*).

In group A1, if the number of deaths is  $\leq 24$  (40%),  $\leq 19$  (32%),  $\leq 13$  (22%) or  $\leq 8$  (13%) out of 60 participants, the upper bound of the 95%CI will be  $\leq 55\%$ ,  $\leq 45\%$ ,  $\leq 35\%$  and  $\leq 25\%$ , respectively.

In group A2, if the number of deaths is  $\leq 54$  (45%),  $\leq 42$  (35%),  $\leq 31$  (26%),  $\leq 20$  (18%) out of 120 participants, the upper bound of the 95%CI will be  $\leq 55\%$ ,  $\leq 45\%$ ,  $\leq 35\%$  and  $\leq 25\%$ , respectively.

In group C, if the number of deaths is  $\leq 17$  (38%),  $\leq 13$  (29%),  $\leq 9$  (20%),  $\leq 5$  (11%) out of 45 participants, the upper bound of the 95%CI will be  $\leq 55\%$ ,  $\leq 45\%$ ,  $\leq 35\%$  and  $\leq 25\%$ , respectively.

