### 9.3 *Intermediate analyses and stopping rules for futility*

**Futility:** In group A1, two intermediate analyses of mortality are planned after the 20th and 40th definitively included patients reaches Day-14 (or die prior to Day-14), respectively. Recruitment in group A1 will be stopped if the results show that the trial is unlikely to prove that mortality with favipiravir is <55%. The DSMB will be in position to recommend to stop inclusion in group A1 for futility if the number of deaths is  $\geq 14$  among first 20 patients, and  $\geq 22$  among first 40 patients in group A1.

In group A2, five intermediate analyses of mortality are planned after 20, 40, 60, 80 and 100 definitively included patients reach Day-14 (or died prior to Day-14), respectively. Recruitment in group A2 will be stopped if the results show that the trial is unlikely to prove that mortality with favipiravir is <55%. The DSMB will be in position to recommend stopping inclusion in group A2 for futility if the number of deaths is  $\geq 14, 22, 29, 36$  and  $44$  among first 20, 40, 60, 80, and 100 patients, respectively.

In group C, four intermediate analyses of mortality are planned after the 10, 20, 30 and 40 definitively included patients reaches Day-14 (or die prior to Day-14), respectively. Recruitment of children will be stopped if the results show that the trial is unlikely to prove that mortality with favipiravir is <55%. The DSMB will be in position to recommend stopping inclusion in group C for futility if the number of deaths is  $\geq 10, 14, 18$  and  $22$  among first 10, 20, 30 and 40 patients, respectively.

**Toxicity:** The Mereva CTU (*see section 8*) will make available to the DSMB members a day-by-day-standardized report of the number of patients included, dead, and alive at end of follow-up. SAE other than death will be reported to the DSMB on a weekly basis. In addition, the DSMB will receive the results of all biological tests available at each intermediate analysis. The DSMB may decide to carry out an intermediate analysis if the number of observed deaths or SAEs is higher than anticipated.

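### The 89% power stated for group A1 is not the power of the planned exact-interval rule, which is 83%

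*Protocol*

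**What the plan says.** Section 6.3 bases the sample size on group A1. It fixes the reference value ("we set the pre-trial mortality to 55% for groups A1, A2, C") and then makes the protocol's only power statement, which refers to A1 at its planned size of 60. The claim reads: "mortality in the trial will be -20% inferior to pre-trial mortality will be equal to 89" per cent. The section names no method for this figure and does not say whether the 20% is absolute or relative. The same section closes recruitment in every group once A1 reaches 60.

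Section 9.1 fixes the analysis: "Mortality at Day-14 will be reported with its exact 95% confidence intervals (CI), overall, and separately by groups (A1, A2, C"). The decision rule there is that "we will conclude that favipiravir decreases mortality if the upper bound of the 95% CI does not include the observed pre-trial mortality". For A1 the section translates this into 24 or fewer deaths out of 60 for an upper limit of at most 55%.

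The synopsis states the same interval rule but prints a strict inequality for the death count: "In group A1, if the number of deaths is <24 (40%) out of 60 participants, the upper bound of the 95%CI will be <55" per cent. It does the same for A2 (54 of 120) and C (17 of 45), where section 9.1 has 54 or fewer and 17 or fewer.

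**The concern.** Power belongs to a particular test. Here the test is fully specified by the exact interval and the 55% reference, and the protocol itself reduces it to a death count. Power at any assumed mortality is then a single binomial probability, and for a 20-point reduction it does not come to 89%.

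This matters because 89% is the only power given, and the number it supports, 60 in A1, ends recruitment for all patients. With no control arm, the death-count threshold and its operating characteristics carry the inference. Anyone weighing a negative result in A1 would take the risk of a missed 20-point benefit to be 11%.

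The two printings of the cut-off add a smaller problem. A result of exactly 24 deaths is a success in section 9.1 but lies outside the count printed in the synopsis.

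**Working it through.** **Inputs**

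- n = 60 in A1 (section 6.3).
- Reference mortality p0 = 0.55 (section 6.3).
- Alternative p1 = 0.55 − 0.20 = 0.35, reading the 20% as absolute.
- Rule: upper limit of the exact two-sided 95% interval below 0.55 (section 9.1), in effect a one-sided test at 2.5%.

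**Reproducing the stated figure**

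One-sample normal approximation, two-sided 5%, no continuity correction:

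Power = Φ( [0.20 − 1.96·√(0.55·0.45/60)] / √(0.35·0.65/60) )
= Φ( [0.20 − 1.96·0.0642] / 0.0616 )
= Φ(1.204) = 88.6%, which rounds to 89%.

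With a continuity correction the same formula gives 85.7%. With the 20% read as relative (p1 = 0.80·0.55 = 0.44) it gives 40.2%, so the 89% can only have come from the absolute reading.

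**Power of the planned rule**

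The exact (Clopper-Pearson) upper limit for x deaths out of 60 is the 0.975 quantile of Beta(x+1, 60−x). Power is P(X ≤ x) for X ~ Binomial(60, 0.35); one-sided type I error is P(X ≤ x) for X ~ Binomial(60, 0.55).

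| Largest count allowed | Upper limit | Below 55%? | Power at 35% | Type I error at 55% |
|---|---|---|---|---|
| 23 (synopsis sign, literally) | 51.8% | yes | 75.3% | 0.7% |
| 24 (section 9.1) | 53.5% | yes | 82.9% | 1.4% |
| 25 | 55.1% | no | 88.7% | 2.6% |

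The largest count that passes is 24, which confirms the cut-off in section 9.1. Its power is 82.9%, so the type II error is 100 − 82.9 = 17.1%, against 100 − 89 = 11% as stated. A count of 25 would restore 89%, but it fails the interval rule and its one-sided error exceeds 2.5%.

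**Effect of the futility looks.** Stopping A1 at 14 or more deaths in the first 20, or 22 or more in the first 40 (section 9.3), lowers power only from 82.9% to 82.8%.

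**Relative reading under the exact rule.** At p1 = 0.44, P(X ≤ 24) = 31.2%.

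**The synopsis cut-offs.** The percentages printed beside them are those of the boundary counts: 24/60 = 40%, 54/120 = 45%, 17/45 = 38%. All three boundary counts pass the interval rule, with upper limits of 53.5%, 54.4% and 53.5%. The probability of exactly 24 deaths in A1 is 82.9 − 75.3 = 7.6% at 35% mortality, and 10.5% at 40% mortality.

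**The case against.** The 89% is not a slip in calculation. It is what a standard approximation gives, planning by approximation and analysing exactly is common, and section 6.3 does not claim an exact figure. The corrected 83% is still above the customary 80%, and the protocol states no target power that it would miss. The exact rule errs on the safe side, with a one-sided type I error of 1.4%. All of this stands, and it means the design is not undermined. It does not make the sentence right: the figure is presented as the power to reach the trial's conclusion, and the rule that produces that conclusion is specified exactly in the same document. A gap of 6 points is more than rounding.

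On the synopsis, the objection is stronger. Its sentence is literally true, since fewer than 24 deaths does give an upper limit below 55%, and the interval rule stated alongside it admits 24 deaths. The printed 40% shows that 24 or fewer was meant. So the 75.3% applies only if the printed sign replaces the interval rule, and the mismatch of signs is close to editorial.

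The relative reading is not a serious rival either, because 89% itself points to the absolute one. It is still worth removing the ambiguity in the text.

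**Conclusion.** The concern holds. Under the protocol's own decision rule, the power in A1 for a true mortality of 35% is 82.9%, about 6 points below the stated 89%, and the risk of missing that effect is 17.1% rather than 11%. The fault is a mismatch between the method used for power and the exact analysis planned. The result rests on n = 60, a fixed 55% reference, an absolute 20-point reduction and the exact two-sided 95% interval; only the absolute reading of the 20% is an inference. The differing inequality signs in the synopsis are a secondary inconsistency, to be corrected at the same time.

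**What to change.** In section 6.3, replace the power sentence with one that names the rule and the alternative, for example: with 60 participants in group A1 and success defined as 24 or fewer deaths (upper limit of the exact 95% CI below 55%), power is 83% if true mortality is 35%, an absolute reduction of 20 percentage points.

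In the synopsis, change the strict inequalities for A1, A2 and C to 24 or fewer, 54 or fewer and 17 or fewer, to match section 9.1.

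This costs wording only; sample size, analysis and stopping rules stay as they are, and the stated power becomes less favourable. If 89% was a real requirement, 60 does not meet it under the exact rule. Sixty-five participants with a cut-off of 27 deaths would give 89.1%, but exact power does not rise steadily with n (66 gives 87.1%), so any new size should be checked directly.
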